#### 2.5.2. Pre-Service ECEs

The program coordinators and early childhood education instructors at participating colleges/universities will be given recruitment materials to distribute to their pre-service ECEs (including the link to the baseline survey). Prior to completing the baseline survey, pre-service ECEs must read the letter of information and consent. Voluntarily beginning the baseline survey will signify their consent to participate in the study. Programs and instructors will be invited to integrate the e-Learning course itself into their course (i.e., by providing class time to complete the course, if appropriate and available). Pre-service ECEs’ participation in the research study itself (i.e., surveys and interviews) will be voluntary (i.e., if pre-service ECEs opt not to participate, they can still access the e-Learning course if their instructor integrates this into class time). 

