### 2.5. Recruitment and Allocation

#### 2.5.1. Universities and Colleges with ECE Programs

To help ameliorate potential recruitment challenges and secure a diverse sample with representation from a number of Canadian provinces, we will draw on our established rapport with early childhood education post-secondary programs and will purposefully select colleges/universities (see sample size explanation below) and recruit their ECE programs to participate by emailing ECE program coordinators. Once 16 colleges agree to participate, allocation to the experimental and comparison conditions will occur. To safeguard the internal validity of the intervention, it is important to avoid randomly allocating individuals within each college to receive the training (or not), given the e-Learning course may be completed during pre-service ECEs’ class time and contamination may occur. As such, participating colleges/universities will act as the unit of randomization (i.e., clusters). Once consent has been obtained from the college/university representative (e.g., program coordinator/chair), the clusters will be stratified by province, college/university size, and college/university ECE program delivery mode (i.e., in-person, online, or blended learning). Blocked randomization will be performed to allocate clusters (1:1) using a computer-generated randomization tool (www.randomizer.org (accessed on 12 March 2022); the software will generate a number of 1 or 0) to either receive the training (experimental; “1”) or not (comparison; “0”).

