### 2.8. Intervention Conditions

#### 2.8.1. Experimental Condition

At colleges/universities assigned to the experimental condition, participating pre-service ECEs will be required to complete the 4-module e-Learning course (in-class or at home, up to the instructor’s discretion) within a 4-week timeframe.

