#### 2.8.2. Comparison Condition

Colleges/universities assigned to the comparison group will continue their typical curriculum for the duration of the study. Upon completion of the study, students in the comparison group may opt to offer the e-Learning course to their pre-service ECEs. Pre-service ECEs in the comparison group will complete the same study instruments as those in the experimental group (with the exception of the process evaluation survey and interviews).

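### As section 2.5 reads, colleges are randomised before their students are invited, and staff who can know the arm do the inviting, so who enrols can depend on arm

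*Protocol article*

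**What the plan says.** Section 2.5.1 gives the trigger for randomisation: "Once 16 colleges agree to participate, allocation to the experimental and comparison conditions will occur". The only consent it asks for first is the institution's: "Once consent has been obtained from the college/university representative (e.g., program coordinator/chair), the clusters will be stratified by province". The unit randomised is the college or university. (The 16 here disagrees with the 18 in the abstract and section 2.1. That is a separate matter.)

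Section 2.5.2 describes how students enter: "The program coordinators and early childhood education instructors at participating colleges/universities will be given recruitment materials to distribute to their pre-service ECEs". Those materials include the baseline survey link, and "Voluntarily beginning the baseline survey will signify their consent to participate in the study". The same section adds: "Programs and instructors will be invited to integrate the e-Learning course itself into their course". It also says that students who decline the research can still take the course where their instructor has put it into class time.

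The arms ask different things of a student who joins. In the experimental arm (section 2.8.1), "participating pre-service ECEs will be required to complete the 4-module e-Learning course". In the other (section 2.8.2), "Colleges/universities assigned to the comparison group will continue their typical curriculum for the duration of the study", and students complete the surveys only.

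Sections 2.12 and 2.12.1 plan baseline tests between groups and adjustment for measured differences where these are found.

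**The concern.** Randomising colleges makes the colleges comparable in expectation. It makes the analysed students comparable only if they enter independently of arm. If students are invited after allocation, by people who know it, the decision to enrol becomes a post-randomisation event that the arm can influence.

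The traits likely to drive volunteering, such as interest in physical activity or confidence in leading it, lie close to the two primary outcomes, self-efficacy and knowledge. They may also affect who is still responding at 3 months. The baseline self-efficacy score is a self-report, so a student who already knows that a course is coming may answer it differently. That would distort the very measure used to check and correct the balance between arms. A larger sample does not reduce either effect.

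**Working it through.** The main check is a reading of the sequence, followed by one piece of arithmetic on expected uptake.

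**1. What must happen before allocation?** Section 2.5.1 lists two events: colleges agree, and a representative consents. Student identification, student consent and the baseline survey are not on the list.

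**2. Is student entry placed earlier anywhere?** No. Section 2.5.2 refers to participating colleges, which exist as such only after step 1, and gives no date for the survey relative to allocation. Appendix C gives indirect support. It schedules recruitment of student champions from intervention classrooms for Fall 2021, and the demographics survey taken before implementation for Winter 2022. On that timetable the arms are known before the survey. Section 2.11 has since moved full-scale implementation to September 2022, so this supports the order of events but not the dates.

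**3. Would the inviters know the arm?** Section 2.5.2 does not limit the request to integrate the course to one arm. Section 2.8.2 keeps comparison colleges on their usual curriculum until the study ends, so the request can apply only to experimental colleges during the trial. Staff asked to schedule the course know their arm. Whether they know it on the day they send the survey link is inferred.

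**4. Does joining mean something different by arm?** Partly. A participant in the experimental arm has a required course and, per Appendix C, a certificate that can go on a resume. A comparison participant has surveys. Where the course is integrated into class, it is open to non-participants too, so the contrast in the offer is smaller there. Where it is not integrated, the article promises non-participants no access.

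**5. What safeguards are stated?** Cluster allocation is justified in section 2.5.1 by contamination, which is a different threat. The article describes no independent recruiter, arm-neutral invitation or student list fixed before allocation. Interest in this kind of education is measured at baseline (section 2.10.1). It is not among the covariates named in sections 2.12 and 2.12.1, although the list in 2.12 is given as examples.

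**6. How much room is there for selection?** The plan's own figures, from section 2.7:
- Design effect: 1 + (164 − 1) × 0.05 = 9.15, as stated.
- Target per group: 112 × 9.15 / 0.70 = 1464, as stated.
- Per college, with 9 colleges per arm: 1464 / 9 = 162.7, about 163 against an average class of 164.

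The target therefore presumes almost complete enrolment. The article gives no expected uptake by arm and no link between willingness to enrol and outcome, so a bias cannot be computed from it.

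**The case against.** The strongest reply has four parts.

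*The order and the staff's knowledge are inferred.* This is correct. No sentence dates the invitation relative to allocation or says when colleges learn their arm, and the letter of information is not shown. The point therefore has to be worded as the natural reading. It stands because the article does fix the allocation trigger, and that trigger leaves student entry out.

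*Research consent is not always the gate to the course.* This is also correct where instructors integrate it, and it weakens the contrast between arms without removing it.

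*Repeated measures and adjustment deal with it.* A stable difference in level already present at baseline largely cancels in a baseline-adjusted or change comparison. What remains is any link between selection and change, unmeasured motivation, and baseline answers given with the arm known. Adjustment helps only in part.

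*At about 163 of 164 per college there is hardly anyone left to select.* If that were achieved, selection would indeed be small. But 1464 is a target and participation is voluntary, so the design should not rely on it.

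A reader might go the other way and infer that most students decline, because the earlier national survey cited in the Background had 1292 respondents at 61 colleges, far fewer per college than 164. The document does not support that inference. Those are responses per college in another study with an unseen number invited, which is not a refusal rate.

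**Conclusion.** The concern holds as a design risk. As sections 2.5.1 and 2.5.2 read, allocation precedes student consent and baseline, and the inviting is done by staff who, in experimental colleges, also have the course to run. Enrolment and baseline self-reports can depend on arm, and the planned adjustment is only a partial remedy.

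Two stronger readings are not supported. One is that the arms will in fact be imbalanced: the document shows an opening for bias and no imbalance. The other is that the bias can be put at some fraction of the effect the trial is sized to detect. Any such figure would rest wholly on assumed uptake and correlations, and would describe an unadjusted comparison. Even the direction is open. The course might attract the keener students, or a class-based push might bring in more of the less keen.

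The conclusion rests on the inferred order of events. If the full protocol completes the baseline survey before colleges learn their arm, the point reduces to a request to say so in the article. Otherwise it is a cheap improvement that should be made.

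**What to change.** In section 2.5, state the sequence explicitly:
1. Colleges agree and their representatives consent.
2. Student consent and the baseline survey open and close at all colleges, with one identical invitation that does not reveal or depend on arm. The letter of information describes both possible conditions.
3. Allocation is generated, or at least released, only after that window closes.
4. The 4-week course starts in the experimental colleges.

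Report, by college and arm, how many students were invited and how many started the baseline survey.

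The cost is mainly scheduling. Every college, including those that will end up in the comparison arm, must hold a provisional slot for the course, and all learn their arm a few weeks later. This cuts against the early planning with staff that Appendix C relies on. Section 2.1 says ethics approval for the full-scale study is still to be sought, so the letter can be worded accordingly at that stage. If holding slots proves unworkable, a weaker alternative is for someone unaware of the allocation to send identical invitations in both arms, with the same reporting of numbers.

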#### 2.5.3. ECE Instructors

Instructors at colleges/universities will be emailed a recruitment letter to ask if they would like to review the e-Learning course and provide their feedback about its content, functionality, and feasibility for the post-secondary early childhood education setting via a process evaluation survey and optional interview.

### 2.6. Inclusion and Exclusion Criteria

#### 2.6.1. Universities and Colleges with Early Childhood Education Programs

Canadian universities and colleges that offer an early childhood education program, where the pre-service ECEs are English-speaking, the program coordinator/chair agrees to the participation of their institution, and instructors are willing to participate, will be eligible to participate in this study.

#### 2.6.2. Pre-Service ECEs

English-speaking individuals who are enrolled in any early childhood education program (regardless of year of study or program type) within a participating Canadian university or college will be eligible to participate.

#### 2.6.3. ECE Instructors

English-speaking instructors who are employed within an early childhood education program allocated to the experimental group will be eligible to participate.

### 2.7. Sample Size

We used the ‘pwr’ package in R [38,39] to estimate the sample size for the analyses (Primary Objectives #1 and #2). These calculations suggest that we need 224 pre-service ECEs (112 per group) to detect a small-to-medium effect size (f^2^ = 0.053 or R^2^ = 0.05), with 2 groups (intervention and control) and 3 time-points (baseline, post-intervention, follow-up), 80% of the time, with an alpha of 0.025. As we will target college/university programs as units (clusters), the sample size will be adjusted to account for the clustering effect, where: D = design effect; *k* = anticipated cluster size (class size in this case); and *ρ* = the intra-cluster correlation coefficient, a measure of the degree of homogeneity among cluster subjects for a particular outcome investigated.
D = 1 + (*k* − 1) *ρ* = 1 + (164 − 1) (0.05) = 9.15

We estimate an average class size of 164 pre-service ECEs (based on our nationwide study of pre-service ECEs from 61 colleges; [19]). Based on a preliminary scan of early childhood education programs in Canada, programs across the country have comparatively similar curriculum; therefore, the intra-cluster correlation coefficient will be lower. For the purpose of estimating this sample size, we assumed a value of 0.05. Thus, the design effect is 9.15, and the sample size needs to be inflated. Finally, the sample will be further adjusted to account for loss to follow-up at 3 months (~30% attrition rate); therefore, the final targeted sample size will be 112 × 9.15/0.70 = 1464 ECE students per group.

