### 1.2. Study Objective

The primary objectives of the Training pre-service EArly CHildhood educators in physical activity (TEACH) study are to examine if the e-Learning course increases pre-service ECEs’: 1. self-efficacy to engage children in physical activity and outdoor play, and minimize sedentary behaviour in childcare; and, 2. physical activity and sedentary behaviour-related knowledge. The secondary objectives of the study are to explore: 1. pre-service ECEs’ behavioural intention and perceived behavioural control to promote physical activity and outdoor play and minimize sedentary behaviour in childcare; and, 2. implementation (e.g., fidelity, feasibility, acceptability, pre-service ECEs’ and early childhood education program instructors’ experiences) and potential scalability (via the Consolidated Framework for Implementation Research (CFIR) checklist) of the e-Learning course. 

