#### 2.12.1. Primary Outcomes

Pre-service ECEs’ physical activity and sedentary behaviour-related self-efficacy and knowledge will be evaluated using two (self-efficacy, knowledge) linear mixed effects models wherein group and time are our primary fixed effects. Demographic variables will be used as predictors of pre-service ECEs’ self-efficacy, knowledge, and behavioural intention and perceived behavioural control in our analyses. Specifically, we will explore the extent to which province/territory predicts the dependent variables, and whether there is a significant effect of previous training, early childhood education program type, and mode of delivery. Based on previous research, the pre-service ECE population is largely female [19], so gender-based differences will not be explored. Finally, if baseline differences are observed, we will include student age, physical activity, and sedentary time as covariates in all models. 

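### The 0.025 alpha in section 2.7 reads as a fixed split of 5% over two primary outcomes; Holm's step-down at the same overall 5% would be more powerful with the same sample

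*Protocol article*

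**What the plan says.** Section 1.2 names two primary objectives: "self-efficacy to engage children in physical activity and outdoor play, and minimize sedentary behaviour in childcare; and, 2. physical activity and sedentary behaviour-related knowledge".

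Section 2.7 uses a single calculation "to estimate the sample size for the analyses (Primary Objectives #1 and #2"). It assumes a "small-to-medium effect size (f^2^ = 0.053 or R^2^ = 0.05"), "with 2 groups (intervention and control) and 3 time-points (baseline, post-intervention, follow-up"), to be detected "80% of the time, with an alpha of 0.025". The result is that "we need 224 pre-service ECEs (112 per group") before inflation for clustering and attrition. This is the only significance level in the article.

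Section 2.12.1 plans "two (self-efficacy, knowledge) linear mixed effects models wherein group and time are our primary fixed effects". It gives no significance level, no multiplicity procedure and no rule for what counts as success. Section 2.9.1 says that separate composites will be calculated for task and barrier self-efficacy.

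**The concern.** The article has two primary outcomes, one model for each, and an alpha of 0.025. An F-test has no one-sided form that would explain 0.025, so the natural inference is 5% divided equally between the outcomes.

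If each outcome is then tested at a fixed 0.025, some error rate goes unused. Suppose knowledge gives p < 0.001 and self-efficacy gives p = 0.03. The fixed split declares self-efficacy negative. Holm's rule compares the smaller p-value with 0.025 and, if that is significant, the larger with 0.05. It would declare both positive, with the same 5% bound on the overall error. The course is meant to improve both outcomes, so the result on the second one is of real interest.

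**Working it through.** **Inputs from section 2.7.** f² = 0.053 (R² = 0.05, and 0.05/0.95 = 0.0526), alpha 0.025, power 80%, 2 groups, 3 time-points, N = 224. The numerator df are not stated. The group-by-time value, u = (2 − 1)(3 − 1) = 2, is inferred because, of u = 1 to 5, only it reproduces 224 at alpha 0.025.

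**Reproducing the plan's figures.** Power comes from the noncentral F distribution with u and v = N − u − 1 df and noncentrality λ = f² × N. With u = 2 and alpha 0.025, 80% power needs N = 221 at f² = 0.053, or N = 223 (224 in equal groups) at f² = 0.0526. The inflated figure also reproduces: 112 × 9.15/0.70 = 1464 per group.

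**Power for one outcome at N = 224.** v = 221 and λ = 0.053 × 224 = 11.87. Power is 0.807 at alpha 0.025 and 0.875 at alpha 0.05.

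**Two outcomes, independent test statistics, equal true effects.**
- Both shown, fixed split: 0.807² = 0.65.
- Both shown, Holm (both p ≤ 0.05 and at least one ≤ 0.025): 0.875² − (0.875 − 0.807)² = 0.766 − 0.005 = 0.76.
- A given outcome shown, Holm: 0.807 + (0.875 − 0.807) × 0.807 = 0.86.
- At least one shown, either rule: 1 − (1 − 0.807)² = 0.96.

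**Correlated test statistics.** The article gives no correlation, so 0 to 0.7 is an assumed range. Simulating pairs of F(2, 221) statistics gives:

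| Correlation | Per outcome, fixed 0.025 | Per outcome, Holm | Both, fixed 0.025 | Both, Holm | At least one, either rule |
|---|---|---|---|---|---|
| 0 | 0.81 | 0.86 | 65.2% | 76.2% | 96% |
| 0.3 | 0.81 | 0.86 | 67.5% | 77.3% | 94% |
| 0.5 | 0.81 | 0.85 | 69.5% | 78.6% | 92% |
| 0.7 | 0.81 | 0.85 | 71.9% | 80.0% | 90% |

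The gain in the chance of showing both is 11.0 percentage points at correlation 0 (76.2 − 65.2) and 8.1 at 0.7 (80.0 − 71.9).

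**Error control.** Holm's simulated familywise error was 4.3–4.9% with both nulls true and 4.0–4.5% with one null true.

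**Sensitivity of the chance of showing both, correlation 0 to 0.7.**
- Design effect based on completers per cluster: 164 × 0.70 = 114.8 students, so the effective N is 2 × 1024.8/(1 + 113.8 × 0.05) = 306. The fixed split gives 86–88% and Holm 92–93%.
- Effective N of 224 with about 16 denominator df (18 clusters less 2 arms): the fixed split gives 49–56% and Holm 64–69%.

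The levels move a good deal, but Holm is ahead throughout.

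**The case against.** The strongest objection is that the article never states the rule being improved on. The 0.025 is an input to a sample-size calculation and is equally the first step of Holm for two tests. An analysis plan that is not shown may already contain a step-down rule. This stands, and a reader should not infer that the article binds each outcome to a fixed 0.025. What remains is that 0.025 is the only level given and no step-down is mentioned, so readers will probably apply it to each outcome.

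A second objection is that an equal split controls the overall error, is standard practice and gives simple simultaneous intervals. That is correct, and the point is one of efficiency only.

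A third is that joint success is not the plan's criterion. A reader might infer from the 65–72% that the trial falls short of its stated 80% power. The documents do not support that. Section 1.2 lists two separate objectives, nothing requires both to succeed, and the 80% reproduces as power per outcome. Measured per outcome the gain is more modest, from 0.81 to 0.85–0.86. The chance of at least one success is not affected.

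Finally, the figures presume exactly two primary tests. If the task and barrier composites both count as primary there are three, and both the fixed split and the Holm steps change.

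**Conclusion.** The point holds as a suggestion for improvement. If the primary outcomes are tested at a fixed 0.025 each, as the sizing suggests, the rule is valid but uniformly less powerful than Holm at the same overall 5%. That ordering, and Holm's error control, hold under any correlation between the outcomes.

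The size of the gain is conditional. The headline ranges (0.81 to 0.85–0.86 per outcome; 65–72% to 76–80% for both) need equal true effects at the planning value, the assumed correlation range, 224 effective students, 2 numerator df and large denominator df. The figures of 224 and 1464 stand as stated.

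**What to change.** Keep 0.025 for sizing, so the sample size does not change. State in sections 2.7 and 2.12.1, before outcome data are seen, that the primary outcomes are tested with Holm's procedure at an overall two-sided 5%. With two primary tests, the smaller p-value is compared with 0.025 and, if significant, the larger with 0.05.

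Say at the same place which self-efficacy score is primary. If task and barrier self-efficacy both are, use the three-test steps: 0.05/3 = 0.0167, then 0.05/2 = 0.025, then 0.05. In that case the sizing alpha of 0.025 would no longer match the first step, and the article should say so.

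The cost is a sentence or two, with no extra students or data. Simultaneous confidence intervals are less simple under Holm than under a fixed split, although 97.5% intervals can still be reported for two outcomes. The timing matters: adopting Holm after seeing p = 0.03 on one outcome would not be credible.

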Of particular concern, ECEs have communicated that they lack the self-efficacy needed to confidently facilitate physical activity for young children in childcare [17,18] and have acknowledged that this is primarily due to their limited professional training in physical activity domains, both during post-secondary education [19,20] and on-the-job [21,22]. A recent investigation of the physical activity knowledge, training, and self-efficacy among pre-service ECEs (*n* = 1292) enrolled at 61 Canadian colleges/universities revealed that only ~30% reported receiving physical activity and screen-viewing-specific training in their program and a mere 15% were familiar with national movement guidelines for young children [19]. More positively, pre-service ECEs who reported undertaking physical activity education demonstrated greater self-efficacy to engage young children in appropriate physical activity opportunities [19]. According to Bandura’s Social Cognitive Theory [23], self-efficacy is one of the most important and robust determinants of behaviour. In support of this theory, a recent meta-analysis revealed that task self-efficacy was the strongest psychological predictor of teaching performance [24]. As such, to effectively prepare pre-service ECEs for their work post-graduation, it is critical that their pre-service education scaffolds their development of self-efficacy in relation to a wide range of teaching contexts, including facilitating physical activity and children’s development of physical literacy.

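### The target of 1464 per group treats the whole class as participants: it needs about 99% uptake of a voluntary survey with 18 colleges, and more than the whole class with 16

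*Protocol article*

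**What the plan says.** Section 2.7 starts from an unclustered requirement: "we need 224 pre-service ECEs (112 per group) to detect a small-to-medium effect size" ("f^2^ = 0.053 or R^2^ = 0.05"), "80% of the time, with an alpha of 0.025". It inflates this by a design effect of 1 + (164 − 1) × 0.05 = 9.15, where the anticipated cluster size is explicitly the class size. The 164 is attributed to the team's earlier nationwide survey: "We estimate an average class size of 164 pre-service ECEs (based on our nationwide study of pre-service ECEs from 61 colleges; [19"]). On the ICC: "For the purpose of estimating this sample size, we assumed a value of 0.05". After a 30% attrition adjustment, "the final targeted sample size will be 112 × 9.15/0.70 = 1464 ECE students per group".

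Three other places bear on this:

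- Section 2.1 assigns 9 colleges or universities to each condition. Section 2.5.1 carries out allocation once 16 have agreed.
- Section 2.5.2 has coordinators and instructors pass on recruitment materials and the survey link, and states that "participation in the research study itself (i.e., surveys and interviews) will be voluntary".
- Section 1 describes the earlier survey as covering "pre-service ECEs (*n* = 1292) enrolled at 61 Canadian colleges/universities".

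**The concern.** Attrition after enrolment is allowed for, but non-participation before enrolment is not. With the number of colleges fixed, the headcount target can be met only if nearly every student in an average class joins. The survey from which 164 is taken reached far fewer students per college.

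The practical harm is that 1464 is a poor yardstick. The team could fall well short of it and still have adequate power, or fall further short and not, and the target does not separate the two cases. A null result from a trial with low uptake could then be read as an adequately powered null.

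**Working it through.** **1. Reproducing the plan's figure.** With f² = 0.053, alpha 0.025 and power 0.80, the noncentral F calculation gives a total N of 182, 221 and 248 for numerator df of 1, 2 and 3. The stated 224 fits 2. The article does not state the numerator df, so this is inferred. Then D = 1 + 163 × 0.05 = 9.15, and 112 × 9.15 / 0.70 = 1464. The chain reproduces.

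**2. Uptake implied by the target.**
- 9 colleges per arm: 1464 / 9 = 162.7 per college; 162.7 / 164 = 99.2%.
- 8 colleges per arm: 1464 / 8 = 183 per college; 183 / 164 = 111.6%. The arm holds only 8 × 164 = 1312 students on the stated class size.
- Source survey: 1292 / 61 = 21.2 per college; 21.2 / 164 = 12.9%.

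**3. Cluster size used in the design effect.** After 30% attrition, 0.70 × 164 = 114.8 per college are analysed, so D = 1 + 113.8 × 0.05 = 6.69. Using 9.15 is conservative: it credits full participation with 9 × 114.8 / 9.15 = 112.9 effective students per arm, when the figure is 9 × 114.8 / 6.69 = 154.4.

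**4. Power by recruits per college.** For m recruits at each of C colleges per arm, the effective number per arm is C × 0.70m / [1 + (0.70m − 1) × ICC]. I computed power in two ways:
- the F test with 2 numerator df and f² = 0.053, which ignores cluster df;
- a two-sided t test at alpha 0.025 with 2C − 2 df, using the standardised difference that 112 per arm detects with 80% power (d = 0.414).

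With 9 per arm and ICC 0.05:

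| Recruits per college | Share of 164 | Effective n per arm | Power, no cluster df | Power, 16 df |
|---|---|---|---|---|
| 21.2 | 13% | 78.9 | 63% | 56% |
| 45 | 27% | 112.3 | 81% | 73% |
| 75 | 46% | 132.2 | 88% | 80% |
| 164 | 100% | 154.4 | 93% | 87% |

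The smallest m giving 112 effective per arm is 44.7. With 16 df, 80% is reached at 72 (d = 0.414) or 75 (d = 0.412, from the normal approximation), which is 44–46% of 164.

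**5. Sensitivity to the ICC** (9 per arm, 16 df, d = 0.414):

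| ICC | 21.2 recruits | 45 | 75 | 164 |
|---|---|---|---|---|
| 0.01 | 75% | 96% | 99% | >99% |
| 0.05 | 56% | 73% | 80% | 87% |
| 0.10 | 41% | 51% | 55% | 59% |

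**6. With 8 per arm** (14 df, ICC 0.05), power is about 50% at 21.2 recruits per college and 81% at 164. Reaching 80% then needs about 141–152 recruits per college (86–93% of 164), depending on whether d is 0.414 or 0.412.

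**The case against.** The strongest reply is that missing 1464 need not cost power. The design effect falls as clusters shrink, and taking it at 164 overstates the sample needed. This stands. A reader might infer from the 99% figure that the 80% power depends on near-complete participation. The document's own inputs do not support that: about 45 recruits per college suffice without cluster df, and 72–75 with 16.

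Second, 21 per college should not be taken as what this trial will obtain. How the earlier survey recruited is not described. Here colleges are chosen through existing rapport (section 2.5.1), instructors must be willing to take part (section 2.6.1), class time may be given for the course (section 2.5.2), and student champions are planned to promote course completion (Appendix C). None of this shows high survey uptake, but it makes 13% a low scenario rather than an expectation. This stands too.

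Third, the article does not say how 164 was derived, the selected colleges need not be average in size, and section 2.6.2 admits students from any year and program type. So 164 is not a proven ceiling, and the target cannot be called strictly unattainable with 18 colleges. What remains is that section 2.7 itself equates cluster size with class size and leaves no margin for refusal.

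**Conclusion.** The concern holds for the target and for the way it was built. On the stated class size, 1464 per group needs 99% uptake with 9 colleges per arm and cannot be met with 8. There is no participation allowance, the design effect is taken at the wrong cluster size (9.15 against 6.69, a conservative error), and cluster df are not considered.

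For power the conclusion is conditional. With 9 per arm, ICC 0.05 and 30% attrition, it falls below 80% when recruits per college drop under about 45 (27%), or under about 72–75 (44–46%) with 16 df. At 21 per college it is about 63%, or 56% with 16 df. The assumed ICC matters as much: at 0.10, power is about 59% with 16 df even at full participation, while at 0.01 it is about 75% with only 21 per college.

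These figures rest on equal cluster sizes, the inferred numerator df of 2 (for the F test), a two-sided alpha of 0.025, and a t test on effective sample size as a stand-in for the mixed model.

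**What to change.** Rewrite the sample-size paragraph in section 2.7:

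- Reconcile the number of colleges between sections 2.1 and 2.5.1, and use that number throughout.
- Set the cluster size to expected participants per college, not class size, and compute the design effect at the number analysed (0.70 × recruits).
- State the numerator df, and base power on cluster df.
- Replace the single figure of 1464 with a table of power by recruits per college (for example 21, 45, 75 and 164) and ICC (for example 0.01, 0.05 and 0.10).
- State the working minimum as about 72–75 recruits per college for 9 per arm at ICC 0.05 with 16 df, not 45. Recompute it if the reconciled number is 8 per arm.

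I would not advise estimating the ICC from the 61-college survey. The self-efficacy questionnaire was created by the team because no existing tool met the project's needs (section 2.9.1), and the knowledge tool was built from the course content (section 2.9.2). The article does not show that the survey measured these outcomes.

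The cost is one paragraph and one table. The stated power becomes less favourable at low uptake. No extra enrolment is needed.
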